#### Process Measures

A process evaluation will be conducted to evaluate the implementation process of the intervention to understand potential factors related to implementation that may be associated with observed outcomes. The evaluation includes fidelity and quality of WIFI implementation, as well as users’ attitudes toward the program, which will be evaluated separately for people living with schizophrenia, their family members, and psychiatrists. After completion of the intervention in each randomized community, both quantitative and qualitative process data will be collected from survey samples of people living with schizophrenia and family members to assess their awareness of and responsiveness to the WIFI program.

Quantitative data will be directly collected through the WeChat backstage management system and include information about families’ use of and engagement with the WIFI program. For psychoeducation data, we will collect information on views, downloads, and shares of WOA publications. For peer-support data, we will collect information on chatting topics, number of messages sent, and active users of the WeChat chat group through chat records. For professional support, we will collect information on help-seeking behaviors of families, number of consultations, problems addressed by psychiatrists, etc.

Qualitative information will be collected through online one-to-one video interviews using the video chat function of WeChat. The technology acceptance model will be used to explore perceived usefulness and perceived ease of use of the WIFI program among people living with schizophrenia, family members, and psychiatrists at the end of the intervention [66-69]. People living with schizophrenia and family members will be asked about their feelings and experiences with the WIFI program, such as attitudes, beliefs, and feedback about the program. Psychiatrists will be asked about their exposure to and experiences with each element of the WIFI program in order to find both facilitators and barriers of program implementation at the provider level. All this information will help the research team gain insights into the feasibility and replicability of the program.

### Data Collection and Management

Data are collected from people living with schizophrenia, their family members, and psychiatrists at baseline (months 1-2) and at 4, 6, 8, and 10 months. A pilot study with face-to-face interviews was recently completed with 400 families of people living with schizophrenia prior to the formal WIFI program to test all measures and collect baseline data. For this data collection, all participants will be invited through WeChat to complete questionnaires through an online survey known as Sojump [70]. Sojump provides a series of services including questionnaire design and distribution, data collection, and analysis. In addition, all qualitative information (on process measures) will be collected by online one-to-one interviews through WeChat video chat. Each family will be reimbursed with money for participation each time, which will depend on the completion of their relevant questionnaires (about 20 minutes for the people living with schizophrenia and 45 minutes for the caregivers). The reimbursement will increase by 25% for each successive assessment to reflect participants’ ongoing study commitment. Specifically, participants will receive RMB 35 (US $5) for the baseline measurement, followed by RMB 44 (US $6.25), RMB 55 (US $7.81), RMB 69 (US $9.77), and RMB 86 (US $12.21) for the subsequent assessments. A family will be reimbursed with a total of RMB 289 (about US $41) for completion of all five assessments. Payment will be sent directly to one designated family member through the WeChat money transfer function. The double entry method will be adopted to input data, with the range for data values preset to avoid any wrong input. All data will be safely stored on a disk and managed by a special data specialist. Table 3 provides an overview of all outcome measures and assessment instruments that will be used in this trial.

**Table 3 table3:** Assessment of study outcomes.

Outcome measures		Assessment				
		M_1-2_^a^	M_3-4_	M_5-6_	M_7-8_	M_9-10_
**Caregivers**						
	Knowledge and skill (Knowledge and Skill of Caregiving for Schizophrenia)	Yes	Yes	Yes	Yes	Yes
	Social support (Multidimensional Scale of Perceived Social Support)	Yes	Yes	Yes	Yes	Yes
	Coping (Simplified Coping Style Questionnaire)	Yes	Yes	Yes	Yes	Yes
	Perceived stigma (Perceived Devaluation and Discrimination Scale)	Yes	Yes	Yes	Yes	Yes
	Caregiver burden (Zarit Burden Interview)	Yes	Yes	Yes	Yes	Yes
	Family functioning (Family Adaptation, Partnership, Growth, Affection and Resolve Index scale)	Yes	Yes	Yes	Yes	Yes
	Positive feelings (Caregiving Rewarding Feelings)	Yes	Yes	Yes	Yes	Yes
	Perceived stress (Perceived Stress Scale)	Yes	Yes	Yes	Yes	Yes
	Depression (Patient Health Questionnaire-9)	Yes	Yes	Yes	Yes	Yes
	Anxiety (Generalized Anxiety Disorder Scale-7)	Yes	Yes	Yes	Yes	Yes
**People living with schizophrenia**						
	Symptoms (Brief Psychiatric Rating Scale)	Yes	Yes	Yes	Yes	Yes
	Functioning (Global Assessment of Functioning)	Yes	Yes	Yes	Yes	Yes
	Quality of life (World Health Organization Quality of Life Brief Scale)	Yes	Yes	Yes	Yes	Yes
	Recovery (Recovery Assessment Scale)	Yes	Yes	Yes	Yes	Yes
	Rehospitalization	Yes	Yes	Yes	Yes	Yes
	Depression (Patient Health Questionnaire-9)	Yes	Yes	Yes	Yes	Yes
	Anxiety (Generalized Anxiety Disorder Scale-7)	Yes	Yes	Yes	Yes	Yes
**Potential confounding factors**						
	Social demographic variables	Yes	No	No	No	No
	Clinical variables	Yes	No	No	No	No
	WeChat use intensity (WeChat Use Intensity Questionnaire)	Yes	No	No	No	No
**Cost**						
	WIFI program (bottom-up approach)	Yes	Yes	Yes	Yes	Yes
	Health care utilization (cost dairy)	Yes	Yes	Yes	Yes	Yes
	Productivity loss (sick leave calendar)	Yes	Yes	Yes	Yes	Yes
**Process**						
	Fidelity (quantitative)	No	No	No	No	Yes
	Quality (quantitative)	No	No	No	No	Yes
	Attitudes (qualitative)	No	No	No	No	Yes

^a^M: month.

### Statistical Analysis

We will use mixed-methods analysis for both qualitative and quantitative data collected during each step of the WIFI program. For qualitative data, a grounded theory approach [71] and immersion-crystallization process [72] will be used to assess process implementation and gain deep insights into the feasibility and replicability of the WIFI program. For quantitative data, descriptive analysis will be conducted to describe the characteristics of the participants during the control and intervention periods. Continuous variables will be described by mean (SD) or median (IQR) depending on the shape of the distribution. Categorical variables will be described by number and percentage in each category. For two-group comparisons, the Student *t* test or nonparametric test will be conducted for continuous variables, while the chi-square test or Fisher exact test will be conducted for categorical variables. Multiple imputations will be adopted to deal with missing values.

Treatment effects (WIFI vs control) will be estimated using generalized linear maximum modeling with clusters as a random effect and time as a fixed effect. All of the available measurements (2, 4, 6, 8, and 10 months) will be used, with the baseline values of each outcome as a covariate. This analysis will take into account the within-cluster and between-cluster correlations, as well as any evolution of the intervention effect over time. Statistical analyses will be performed at the individual level and according to the intention-to-treat principle, which will be compared to per-protocol analyses. Additionally, extra costs of the WIFI program will be evaluated.

### Power Analyses

To illustrate the power for analyses of both caregivers and people living with schizophrenia, we can use a baseline ZBI score of 45 for caregivers and a baseline GAF score of 42 for people living with schizophrenia based on previous studies as well as a baseline study conducted by the research team with caregivers and people living with schizophrenia in Hunan province. For a SWCRT with 12 communities over five time periods or steps (baseline and four intervention steps), assuming an intracluster correlation of 0.05, 90% power at a 5% significance level, and 20% dropout ratio, a sample size of 235 is needed to detect a clinically important decrease in caregiver burden as assessed by a decrease in the ZBI score from a baseline of 45 to 30 [50]. Similarly, for people living with schizophrenia, a sample size of 210 is needed to observe an increase in the GAF score from a baseline of 42 to 52, assuming α=.05, β=.15, and 20% attrition. Based on the above calculations, we decided on a sample size of 20 families per community (240 families in total), which will be sufficient to detect expected improvements in both caregiver burden and functioning of people living with schizophrenia.

### Cost-Effectiveness Analyses

A cost-effectiveness analysis will be performed from the societal perspective according to the intention-to-treat approach, with missing data imputed using multiple imputations [73]. CIs (95%) will be obtained by bias corrected and accelerated bootstrapping. The incremental cost effectiveness ratios will be calculated by dividing the differences in mean total costs between both groups by the difference in mean effects between both groups (eg, ZBI score of caregivers and BPRS and GAF scores of people living with schizophrenia). The incremental cost utility ratio will be calculated by dividing the incremental costs by the difference in the quality-adjusted life years assessed with the EuroQoL five-dimensional instrument (EQ-5D) between both treatment groups. These ratios will be graphically presented in a cost-effectiveness plane [74].

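### The cost-effectiveness ratios and their bootstrap intervals carry no term for community or period, unlike the effect model, so intervals would be too narrow if families are resampled as independent units

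*Protocol article*

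**What the plan says.** The Cost-Effectiveness Analyses section of the protocol article defines the incremental cost-effectiveness ratio as "dividing the differences in mean total costs between both groups by the difference in mean effects between both groups". The effects given as examples are "eg, ZBI score of caregivers and BPRS and GAF scores of people living with schizophrenia". For uncertainty it says "CIs (95%) will be obtained by bias corrected and accelerated bootstrapping", and the ratios are to be plotted on a cost-effectiveness plane. The section names no resampling unit, no community effect, no period effect and no coding direction for the scores.

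Other sections treat the data as clustered. Statistical Analysis estimates treatment effects with clusters as a random effect and time as a fixed effect. Power Analyses sizes the caregiver burden comparison "assuming an intracluster correlation of 0.05" and settles on 20 families in each of the 12 communities. Table 1 shows five periods and four crossover groups of three communities.

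**The concern.** Families in one community share a crossover date and, on the protocol's own assumption, are correlated. In its standard form the BCa bootstrap resamples independent units. Applied to families, it sees the variation between families but not the extra variance that arises because whole communities move together. The intervals for incremental cost and effect would then be too narrow.

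The ratio is also written as a plain two-group contrast, although control data come mostly from early periods and WIFI data from late ones.

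Comparing costs is specific aim 2, and a cost-effective model suited to national policy is an expected result in the Discussion. Intervals that are too narrow could support that conclusion on variation between communities alone.

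A smaller point concerns direction. Benefit is a fall in ZBI and BPRS but a rise in GAF, and one ratio rule and one plane serve all three.

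**Working it through.** **The plan's own figure.** The only coverage figure is the nominal 95%. The only calculation that uses the ICC is the 235 for ZBI. It cannot be reproduced, because no standard deviation is given.

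**Inputs from the article.** 12 communities, five periods, four groups of three (Table 1); m = 20 families per community, or 20 × 0.8 = 16 after the planned 20% dropout; ICC 0.05 (Power Analyses).

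**Assumptions.** Families are the resampling unit. The ICC, given for ZBI, also applies to costs. The share of within-community variance that is stable within a family runs from 0 to 0.9. Community effects are either constant over time or have one fifth of the ICC varying by period.

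**Step 1: crude difference in means, as the section defines it.**
- Table 1 gives 3 × (1+2+3+4) = 30 control community-periods and 30 WIFI community-periods. Each observation therefore has weight ±1/(30m).
- The net weight of a community is ±3/30 or ±1/30. The sum of squared community weights is 3 × (9+1+1+9)/900 = 60/900.
- The sum of squared observation weights is 60m/(30m)² = (60/900)/m, which equals the sum of squared family weights.
- The true variance over the variance seen by a family bootstrap therefore reduces to DE = 1 + (m − 1) × ICC, whatever the within-family correlation.
- Coverage = 2Φ(1.96/√DE) − 1.

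| ICC | m | DE | Coverage |
|---|---|---|---|
| 0.05 | 20 | 1 + 19 × 0.05 = 1.95 | 84.0% |
| 0.05 | 16 | 1 + 15 × 0.05 = 1.75 | 86.2% |
| 0.02 | 20 | 1 + 19 × 0.02 = 1.38 | 90.5% |
| 0.02 | 16 | 1 + 15 × 0.02 = 1.30 | 91.4% |

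A BCa simulation of the crude difference (normal data, within-family share 0.5) gave 83.4% (m = 20) and 84.6% (m = 16) at ICC 0.05, and 89% at ICC 0.02 (m = 20).

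**Step 2: other estimators, families still resampled.** The same variance ratio was computed with the weights of each estimator.
- Period-adjusted least squares, ICC 0.05: 75.8-84.5% (m = 20) and 79.2-86.6% (m = 16). BCa simulation at a share of 0.5: 79.1% and 81.2%.
- Period-adjusted least squares, ICC 0.02: 86-92%.
- Differences from a model with community random and period fixed, ICC 0.05, within-family share 0 to 0.7: about 87-94%.

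**Step 3: resampling whole communities.** At ICC 0.05 and a share of 0.5, BCa on the crude difference covered about 88%. Shorter runs of the period-adjusted difference gave about 90-92%. Both fall short of 95% because there are only 12 communities.

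**Step 4: period imbalance.** Numbering the periods 1 to 5, the mean WIFI period is (2×3 + 3×6 + 4×9 + 5×12)/30 = 4. The mean control period is (1×12 + 2×9 + 3×6 + 4×3)/30 = 2. The groups are two periods (four months) apart, so a crude difference absorbs two periods of any calendar trend. The coverage figures above assume no trend.

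**Step 5: direction.** Take an illustrative extra cost of 1000 and the targets in Power Analyses. For ZBI, "a decrease in the ZBI score from a baseline of 45 to 30" is a change of −15, so unreversed scores give 1000/(−15) = −66.7. GAF from 42 to 52 gives 1000/10 = +100. Coded as improvement, ZBI gives +66.7.

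**The case against.** The strongest reply is that this is a condensed article. The resampling unit is a detail that such an article commonly leaves to the full protocol or analysis plan. BCa is a way of building an interval and works equally well on resampled communities or on model estimates. Statistical Analysis shows that the team means to handle clustering, and that section also mentions evaluating the programme's extra costs. This stands as far as it goes: the article does not say that families will be resampled. It does not remove the point, because the article does state the estimator. That is a two-group difference in means, and it differs from the model stated for effects.

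A reader might go further and infer one specific coverage figure near 80%. The documents do not support that. The lower values need a period-adjusted least-squares estimator that no section describes, the ICC is not given for costs, and the within-family correlation is not given at all. The simulations also concern a mean difference; the interval for the ratio itself was not simulated.

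A reader might also infer that the ZBI and BPRS ratios will carry the wrong sign. The section speaks of a difference in mean effects and never says that scores enter unreversed, while the article is clear elsewhere about which direction is benefit. What is missing is a stated convention; an error is not shown.

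Net benefit and acceptability curves would be a matter of preference. Ratios shown on a plane are not a mistake.

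**Conclusion.** The point holds as an inconsistency between stated methods: effects are modelled with community and period, while the cost-effectiveness ratios and intervals are described without either. Its size is conditional. With families resampled and ICC 0.05 applied to costs, nominal 95% intervals would cover roughly 76-87%. For the crude difference, coverage of 84-86% means that a true null would be excluded about 14-16% of the time instead of 5%, and that intervals would need to be √1.75 = 1.32 to √1.95 = 1.40 times as wide. The shortfall is smaller at ICC 0.02 (about 86-92%) or if the effect model supplied the differences (about 87-94%). The powered ZBI and GAF comparisons are not affected. The direction of coding is a clarification only.

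**What to change.** State in Cost-Effectiveness Analyses that incremental cost and incremental effect are both estimated from a model of the kind used for effects, with period fixed and community and family random. Draw their joint uncertainty from that model, for example by parametric bootstrap, and form the ratio and the plane from those draws. Naming a community bootstrap would improve on resampling families but would not be enough with 12 communities. If it were stratified by sequence, with three communities in each, it would capture only (3 − 1)/3 = two thirds of the between-community variance.

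Add one sentence saying that effects are coded so that positive means improvement (reductions for ZBI and BPRS). Unreversed scores would put the same benefit in opposite quadrants for ZBI or BPRS and for GAF.

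The cost is analysis-plan wording, modest programming and wider intervals. Recruitment, data collection and sample size do not change.

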### Design

This study uses a pragmatic stepped-wedge design [44] to evaluate both the effectiveness and implementation strategy of the WIFI program. The CONSORT checklist is presented in Multimedia Appendix 1, and the SPIRIT checklist is presented in Multimedia Appendix 2. We will conduct a multicenter prospective controlled trial, using a stepped-wedge design, comparing the WIFI program integrated into the Reward Policy (intervention group) and the Reward Policy alone (control group) in family caregiving among people living with schizophrenia.

In a SWCRT, all clusters are randomly and sequentially crossed over from control to intervention over a number of time periods [48]. All clusters serve as a control group at the beginning of the study and end up in the intervention group at the end of the study. Compared with traditional randomized controlled trials and parallel cluster studies, a SWCRT enjoys unique ethical benefits since all clusters will ultimately receive the assumingly beneficial intervention at the end of the study [49]. In addition, a SWCRT enables analyses of any temporal effects of the intervention since each cluster acts as its own control and also allows for estimation of both between- and within-cluster effects of the intervention owing to repeated measurements [49]. As a result, a SWCRT design achieves greater statistical power with smaller sample sizes and is more cost-effective than parallel group designs.

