In the proposed study, a WIFI program will be implemented sequentially across an 8-month intervention period in the 12 communities by Changsha Psychiatric Hospital. A total of 20 families will be recruited from each community, leading to a total sample of 240 families. Allocation will be determined by an external statistician using a computer-generated random number sequence. Each number will be secretly and securely stored in a sealed envelope by the external statistician until the intervention starts. The first author (YY) will generate the allocation sequence, the medical team will work on enrolling participants, and the second author ([name]) will assign participants to interventions. The 12 communities will be randomized into four groups according to geographic distance and number of people living with schizophrenia to reduce the risk of contamination and group size inequality. After allocation, each group will be randomized to one of four fixed sequences every 2 months during an 8-month intervention period (Table 1 and Figure 2). All communities will receive the usual financial benefit of the Reward Policy as the control condition before the intervention, and then, successively and in random order, will cross over to the WIFI program at 2-month intervals until the study ends.

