**Figure 2 figure2:**
[figure not shown]
Flowchart for participant recruitment and allocation. C: community; F: family.

**Table 1 table1:** Design of the four-stage stepped-wedge cluster randomized trial.

Cluster community (CM) group^a^	Assessment^b^				
	Baseline (M_1-2_)^c^	Step 1 (M_3-4_)	Step 2 (M_5-6_)	Step 3 (M_7-8_)	Step 4 (M_9-10_)
CM_1-3_	C^d^	WIFI^e^	WIFI	WIFI	WIFI
CM_4-6_	C	C	WIFI	WIFI	WIFI
CM_7-9_	C	C	C	WIFI	WIFI
CM_10-12_	C	C	C	C	WIFI

^a^Number of clusters=12; number of groups=4; number of clusters per group=3.

^b^Step length=2 months; number of participants per step=20.

^c^M: month.

^d^C: control (Reward Policy alone).

^e^WIFI: WeChat-based Integrative Family Intervention.

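### The cost-effectiveness ratios are defined by a two-group formula with no period term, so in this stepped-wedge layout calendar change can be counted as programme effect

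*Protocol article*

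**What the plan says.** The Cost-Effectiveness Analyses section takes a societal, intention-to-treat view with multiple imputation. It forms the incremental cost-effectiveness ratio by "dividing the differences in mean total costs between both groups by the difference in mean effects between both groups", with ZBI, BPRS and GAF as example effects. The cost-utility ratio comes from "dividing the incremental costs by the difference in the quality-adjusted life years", based on the EQ-5D. On uncertainty it says "CIs (95%) will be obtained by bias corrected and accelerated bootstrapping". It mentions neither calendar period nor the mixed model.

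The Statistical Analysis section puts time in as a fixed effect and clusters as a random effect, but for the WIFI-versus-control treatment effects. On costs it says only that the programme's extra costs will be evaluated.

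The Design section describes the crossover: communities, "successively and in random order, will cross over to the WIFI program at 2-month intervals until the study ends". It also states: "All clusters serve as a control group at the beginning of the study and end up in the intervention group at the end of the" trial. The Table 1 footnotes give the layout: "Number of clusters=12; number of groups=4; number of clusters per group=3" and "Step length=2 months; number of participants per step=20".

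**The concern.** A difference in means between two groups suits a parallel trial, where both groups are observed over the same calendar time. Here every community supplies both conditions, control always first. A comparison of condition means is therefore also a comparison of earlier with later months. Any change over the 10 months that is unrelated to WIFI, for example in admissions, leave days or scores, goes into the numerator, the denominator or both.

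The effectiveness analysis guards against this with its time term. The ratios, as defined, do not. The Abstract names these ratios as the cost-effectiveness analysis, and the Discussion expects the study to yield a cost-effective, replicable model.

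A second problem follows from the layout. Families spend different lengths of time in each condition, so a family's total cost under control or WIFI depends partly on its sequence. The article gives no common time unit.

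**Working it through.** The plan gives no figure for this point, so there is none to reproduce. The inputs are the Table 1 layout (four groups of three communities, five 2-month periods) and the planned changes in the Power Analyses section (ZBI 45 to 30, GAF 42 to 52). The size of any background trend is an assumption.

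**1. Calendar position of the two conditions.** Communities in each condition, by period:

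| Period | 1 | 2 | 3 | 4 | 5 |
|---|---|---|---|---|---|
| Control | 12 | 9 | 6 | 3 | 0 |
| WIFI | 0 | 3 | 6 | 9 | 12 |

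- Control mean period = (12×1 + 9×2 + 6×3 + 3×4)/30 = 60/30 = 2.0
- WIFI mean period = (3×2 + 6×3 + 9×4 + 12×5)/30 = 120/30 = 4.0
- Gap = 2 periods × 2 months = 4 months

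If baseline is used only as a covariate, the control mean is (9×2 + 6×3 + 3×4)/18 = 48/18 = 2.67. The gap is then 1.33 periods, or about 2.7 months. With 20% dropout accruing evenly over the five periods, the 4-month gap barely moves (3.99 months).

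**2. Effect of a trend.** For a linear background change *b* per period and true effect *d*, the difference in condition means is *d* + 2*b* with five equally weighted periods, or *d* + 1.33*b* without baseline. With *d* = 0, a least-squares fit with group and period effects returns 0.00 for every trend tried (0.25, 0.5 and 1 point per month, in either direction). The unadjusted difference is 1.0, 2.0 and 4.0 points in size.

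**3. Illustration (assumed favourable trend of 0.5 point per month, so *b* = 1).**

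- ZBI: 15 + 2 = 17. At fixed incremental cost the ratio is multiplied by 15/17 = 0.88, about 12% lower.
- GAF: 10 + 2 = 12. The factor is 10/12 = 0.83, about 17% lower.
- Over the assumed range of 0.25 to 1 point per month, the ZBI difference would be 16 to 19 and the GAF difference 11 to 14.

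An unfavourable trend moves them the other way.

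**4. Time in each condition.** By sequence, control lasts 2, 4, 6 or 8 months and WIFI 8, 6, 4 or 2. The average is 5 months in each, but within a family WIFI minus control is +6, +2, −2 or −6 months. For literal per-family totals, the sum of period numbers under WIFI minus that under control is:

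- 14 − 1 = 13
- 12 − 3 = 9
- 9 − 6 = 3
- 5 − 10 = −5

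The mean is 20/4 = 5. An assumed rise of RMB 100 per family per period would thus add 5 × 100 = RMB 500 to the mean difference in totals. On a per-period scale it would add 2 × 100 = RMB 200.

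**The case against.** The best defence is that the section only repeats the textbook definition of the ratio and does not say how either difference is estimated; the text never says unadjusted. The named effects are trial outcomes, and the Statistical Analysis section assigns treatment effects to a model with time in it. That reading is fair and could rescue the denominator. It does not reach the numerator or the QALY difference, for which no time-adjusted model appears anywhere in the article.

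It is also true that no trend is documented, so no actual bias is shown, and that the 4-month figure depends on all five periods entering equally. Both limits stand.

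A reader might infer four stronger points that the article does not support:

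- **Tests.** The simple tests in the Statistical Analysis section ("nonparametric test will be conducted for continuous variables, while the chi-square test or Fisher exact test will be conducted for categorical variables", and the *t* test) might seem to share the flaw. These tests follow a descriptive passage, the groups compared are not specified, and treatment effects are assigned to the mixed model.
- **Prices.** General price drift is largely handled, because the Cost Measures section converts all costs to 2019 prices with consumer price indices. What remains is drift in service use, leave and scores.
- **Bootstrap.** The resampling unit is unstated, not wrong, and an article may leave it to a fuller plan.
- **Aim 2.** It is worded as a comparison of total cost, not as a ratio, so it does not rest on these ratios.

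**Conclusion.** The point holds for the ratio formula. Followed as written, it compares conditions whose mean calendar positions differ by 4 months (about 2.7 without baseline as an outcome period), and a linear trend enters at about twice its change per 2-month period. This rests on the Table 1 layout with equal community sizes. The direction and size of the real bias cannot be stated, because they depend on a trend the article does not give. The 12% and 17% figures illustrate one assumed trend and are not predictions.

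The most favourable reading leaves costs and QALYs without period adjustment, and total cost without a common time unit. A reader might infer that the effectiveness results are compromised too; they are not on this ground, since that model includes time.

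**What to change.** Amend the Cost-Effectiveness Analyses section as follows:

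1. Express costs and effects per family per 2-month period.
2. Estimate incremental cost and incremental effect as the WIFI coefficients from models with period as a fixed effect and community (and participant) as random effects.
3. Treat QALYs the same way if the EQ-5D is collected each period. It is not in Table 3 at present, so the schedule must be settled first.
4. Form the ratios and the cost-effectiveness plane from these coefficients.
5. Obtain intervals by a method that respects community clustering and the small number of communities, such as a bivariate mixed model or a cluster bootstrap with a small-sample correction. Plain resampling of three communities within each sequence would understate the variance of a sequence mean by a factor of about (3 − 1)/3 = 2/3, so its intervals would be too narrow.

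Table 3 already schedules costs and the listed outcomes at all five assessments, so apart from the EQ-5D no new data are needed. The cost is some extra analysis work and wider intervals.
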